## 5 STUDY POPULATION

### 5.1 Population (base)

Subjects with a high risk of (developing) chronic kidney disease will be recruited in primary care practices and pharmacies from the General Practitioners Research Institute (GPRI) network. The organizational model of GPRI is based on the participation of independent practices and pharmacies in the Netherlands, well-trained GPs, pharmacists and their staff. Male and female subjects of 45-80 years of age that meet the inclusion criteria will be eligible for the study.

### 5.2 Inclusion criteria

#### 5.2.1 Recruitment via pharmacies

- Age of 45-80 years
- Delivered medication within the last 6 months for one of the following indications (available recorded information on indication will be considered):

| Indication                | Medication                                                          | ATC code                |
|---------------------------|---------------------------------------------------------------------|-------------------------|
| Diabetes Mellitus         | Glucose lowering drugs, excluding insulins                          | A10B*                   |
|                           | Other drugs used in diabetes, including aldose reductase inhibitors | A10X*                   |
|                           | Insulin and analogues                                               | A10A*                   |
| Hypertension              | ACE-inhibitors                                                      | C09A, C09B              |
|                           | Angiotensin receptor blocker (ARB)                                  | C09C, C09D              |
|                           | Diuretics                                                           | C03                     |
|                           | Calcium-antagonists                                                 | C08                     |
|                           | Betablockers, excluding propranolol                                 | C07*, excluding C07AA05 |
| Lipid lowering treatments | HMG CoA reductase inhibitors (statins)                              | C10AA, C10BA, C10BX     |
|                           | Ezetimibe                                                           | C10AX09                 |

|  |  |  |
|--|--|--|
|  |  |  |
|--|--|--|

### 5.2.2 Recruitment via general practitioners

- 45-80 years old
- At least one of the following indications (based on ICPC codes and recorded laboratory measurements (e.g., blood pressure)).

| Indication                                                           | ICPC code                                             |
|----------------------------------------------------------------------|-------------------------------------------------------|
| ○ Diabetes Mellitus                                                  | T90.01 & T90.02                                       |
| ○ Obesity (BMI $\geq 30$ kg/m  )                         | T82                                                   |
| ○ Lipid disorders                                                    | T93.0*                                                |
| ○ Hypertension                                                       | K86 (without organ damage)
K87 (with organ damage) |
| ○ Established cardiovascular disease (see indications in rows below) |                                                       |
| 1. Acute coronary syndrome                                           | M80                                                   |
| 2. Angina Pectoris                                                   | K74                                                   |
| 3. Coronary revascularization/coronary sclerosis                     | Surgery                                               |
| 4. Transient Ischemic Attack (TIA) or stroke                         | K89, K90                                              |
| 5. Aorta aneurysm                                                    | K99.01                                                |
| 6. Claudicatio intermittens                                          | K92.01                                                |
| 7. Peripheral revascularization                                      | Surgery                                               |
| 8. (Chronic) ischemic heart disease                                  | K76                                                   |
| 9. Myocardial infarction                                             | K75                                                   |
| 10. Atherosclerosis                                                  | K91                                                   |
| 11. Decompensatio cordis                                             | K77                                                   |

### 5.3 Exclusion criteria

- Inability to understand and sign the informed consent form
- Pregnancy
- Know normal (<3mg/mmol) albuminuria status with 18 months prior

## **5.4 Sample size calculation**

We aim to examine at least 112 patients with elevated albuminuria at the elaborated screening phase in this study. In the pilot study, 57 patients were examined at the elaborated screening phase. In the pilot study, 2 pharmacies and 3 general practitioners were included. For the extension, 3 pharmacies and 7 general practitioners will be recruited. We assume that at least 6300 patients from general practices and pharmacies will be eligible for inclusion in the screening phase.

## **6 TREATMENT OF SUBJECTS**

Not applicable as there are no direct treatment interventions in this study. This is a targeted screening study, in which subjects with an increased risk of elevated albuminuria are identified and screened for albuminuria. If albuminuria is elevated, the CKD/CVD risk factors are assessed, and medication will be reviewed during an elaborated screening visit following standard guidelines. These results will be shared with the subjects' general practitioner.

## **7 INVESTIGATIONAL PRODUCT**

Not applicable

## **8 NON-INVESTIGATIONAL PRODUCT**

### **8.1 Name and description of non-investigational product(s)**

#### **8.1.1 PeeSpot**

Albuminuria will be measured in a laboratory as the urinary albumin-to-creatinine ratio (UACR) using the PeeSpot method. Elevated albuminuria will be defined as a urinary albumin creatinine ratio (UACR)  $\geq 3.0$  mg/mmol (equivalent to  $\sim 30$  mg/g). A confirmatory test using the same methods will be performed in case of elevated albuminuria, because of intra-individual and biological variation, following the Clinical Practice Guideline for the Evaluation and Management of Chronic Kidney Disease (10), except when elevated albuminuria was also previously assessed within 11 months prior to the PeeSpot measurement.

For the PeeSpot measurement, subjects will receive a urine collection device that consists of a tube with an inert absorption felt which is clamped in a holder with handle (17). The absorption felt has the property to absorb urine well and quickly. After centrifugation all

substances are obtained again from the felt with 100% recovery (17,18). The utility of the PeeSpot is tested in multiple studies, where the PeeSpot was found to be reliable and suitable for chemical analyses of urine samples (17). In order to use the PeeSpot, subjects need to open the tube and take the PeeSpot out. Subjects need to urinate over the absorption felt for about five seconds and place the PeeSpot back in a leakproof tube and firmly close the lid. The PeeSpot can be sent in a 'medical package' envelope to the laboratory. The tube is centrifuged in the laboratory and the urine obtained is suitable for all biochemical tests. Subjects find the PeeSpot easy to use (17).

### **8.1.2 Abbott Affinior™ HbA1c**

During the screening visit, where CKD/CVD risk factors will be assessed, HbA1c will be measured with a point-of-care-test (Afinior™ HbA1c). The HbA1c-level of the subject is measured within three minutes using a couple drops of (capillary) blood of the subject.

### **8.1.3 Abbott i-STAT Alinity handheld analyser**

Creatinine will be measured with a point of care i-STAT Alinity handheld analyser (Abbott). This system operates with the i-STAT Alinity Creatinine (CREA) cartridges. A drop of blood is applied on the cartridge, followed by insertion in the machine. This machine provides current creatinine measurements in two minutes.

## **8.2 Dosages, dosage modifications and method of administration**

Not applicable.

## **8.3 Preparation and labelling of non Investigational Medicinal Product**

Not applicable.

## 9 METHODS

### 9.1 Study endpoints

#### 9.1.1 Primary endpoints

1. Elevated albuminuria, defined as a urinary albumin creatinine ratio (UACR)  $\geq 3.0$  mg/mmol.
2. Average screening costs per subject that was identified as having kidney disease by screening for albuminuria. All costs considered are mentioned below (Table 1)

Table 1. Costs associated with screening

|                                                                             |
|-----------------------------------------------------------------------------|
| Costs of the PeeSpot                                                        |
| Laboratory costs                                                            |
| Printing and postal mailing costs of all invitations and needed information |
| Labor costs needed to recruit and start GP's and pharmacies                 |
| Labor costs of training GP's and pharmacies                                 |
| Costs of extracting patients eligible for inclusion                         |

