**Study methods:** For this study subjects will be recruited for a targeted screening via pharmacies and general practitioners. For the pharmacies, subjects at risk of albuminuria will be identified as those with a prescription for Diabetes Mellitus, hypertension or lipid disorders. For general practitioners, subjects who have Diabetes Mellitus, cardiovascular disease, hypertension, lipid disorders, or obesity will be selected from electronic medical records. For the targeted screening, subjects are asked to collect urine at home for an albuminuria measurement. In case of elevated albuminuria, subjects will receive a second collection device for a confirmational measurement. If elevated albuminuria is confirmed, subjects will be invited for an elaborated screening visit. Elevated albuminuria will be defined as an urinary albumin creatinine ratio (UACR)  $\geq 3.0$  mg/mmol on two occasions in accordance with the prevailing primary care guideline ("NHG Standaard Chronische Nierschade"). If not confirmed, they will receive a third collection device. If the third collection device shows normal albuminuria, the study ends. In case of elevated albuminuria, subjects will be invited for an elaborated screening visit. During this screening visit, cardiovascular risk factors will be assessed, and medication use will be reviewed. A review report following the Dutch primary care guidelines will be provided to the subjects' general practitioner (GP). We aim to examine at least 112 patients with elevated albuminuria at the elaborated screening phase in this study. In the pilot, 57 patients with elevated albuminuria were screened in the elaborate screening phase. These patients were included from 2 pharmacies and 3 general practitioners. For the proposed extension, the pharmacies will be scaled up to a total of 5 and general practitioners to a total of 10. Six months after the study

visit, the frequency of cardiovascular monitoring and treatment changes via medication prescriptions will be monitored via data extraction of the general practitioners and/or pharmacies.

We assume that at least 6300 patients from general practices and pharmacies will be eligible for inclusion in the screening phase.

The costs of both screening approaches per identified patient with elevated albuminuria will be evaluated and compared.

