asked to collect urine using the PeeSpot and to send this to GPRI by postal mail for a measurement of albuminuria in the laboratory. Subjects will be informed about the results and, only in case of elevated albuminuria levels, the subject will be asked to repeat the procedure for a confirmational measurement. If the confirmational measurement is negative, a third measurement is needed. If recent (<11 months ago) albuminuria levels were available from the general practice and found to be elevated as well, a second confirmational PeeSpot measurement will not be needed. If recent albuminuria levels recorded by the practice were not elevated, subjects will be considered as not having elevated albuminuria and will be included in the calculation of the prevalences but will not be approached to participate. When albuminuria is confirmed, treatment status will be reviewed, and cardiovascular risk factors will be assessed during a visit. Measurements performed during this visit are non-invasive and part of standard care in general practice and therefore not associated with additional risks. A benefit for the subject could be that elevated albuminuria may be detected earlier because of the screening, and thus comes with health benefits, such as adequate treatment of impaired renal function and medication monitoring by the pharmacy, which has been proven to be effective in preventing adverse events of medication.

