#### Albuminuria screening using PeeSpot

Selected subjects will receive an invitation to participate in the screening survey from their pharmacy or general practice by postal mail, including an informational letter about the study, an informed consent form, a short questionnaire to be completed (Appendix 16.1)

and a urine collection device (PeeSpot) with instructions. The participant will be asked to send the signed informed consent form and completed questionnaire and the collected urine to the General Practitioners Research Institute (GPRI) by postal mail (without costs). If the laboratory measures 'normal' albuminuria ( $<3.0$  mg/mmol), GPRI will inform the subject. In case of elevated albuminuria ( $\geq 3.0$  mg/mmol), GPRI will be informed to send a second PeeSpot for a confirmational measurement if informed consent has been received. If this second measurement is also elevated ( $\geq 3.0$  mg/mmol), subjects will be invited for an elaborated screening visit performed by GPRI (phase 2). A second confirmational measurement of elevated albuminuria will not be required when a recent (within 11 months) measurement performed by the general practice also indicated elevated albuminuria.

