#### **4.2 Phase 2: Elaborated screening phase**

When there is no elevated albuminuria at phase 1, a letter with the results will be sent to the participant, and no further actions from the participant are required. Subjects will be carefully informed about the results.

When elevated albuminuria is confirmed ( $\geq 3.0$  mg/mmol on two occasions), subjects are invited for an elaborated screening visit with a researcher. At the start of the visit, participants will be asked to provide informed consent. Next, CKD/CVD risk factors will be assessed and the participant's medication use, and medication adherence will be reviewed during an interview. GPRI will produce a report of their findings which will be shared with the general practice, including recommendations for additional measurements or treatment changes if applicable.

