### Targeted screening phase

Pharmacies and GPs select potential subjects based on the medical history and last 6 months of prescriptions and registered indications, as described in section 5.2. During this phase subjects will be asked to give written informed consent to participate in the study. Subjects will collect urine samples using the PeeSpot and sent the samples to the laboratory. Furthermore, they receive a questionnaire to collect subject characteristics. The informed consent form and the subject characteristics questionnaire are sent to the General Practitioners Research Institute (GPRI). GPRI will receive the results of the urine tests. If albuminuria is elevated, subjects receive a second PeeSpot to perform a confirmational measurement. If subjects are recruited via GPs and have an elevated albuminuria measurement performed less than 11 months ago, only one extra albuminuria measurement is necessary.

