## **11 STATISTICAL ANALYSIS**

Characteristics of subjects recruited will be described as mean values with standard deviation or median with interquartile range for continuous variables. Categorical variables will be described as numbers and percentages of the subjects per category.

The overall prevalence of elevated albuminuria, and prevalences of unrecognized and persistent elevated albuminuria despite a RAS-inhibitor are described as percentages with 95% confidence intervals. The number of eligible patients from general practices who fulfilled the inclusion criteria but had an albuminuria level  $<3$  mg/mmol recorded within 18 months prior to selection (and where therefore not invited to participate), will be included in the denominator to calculate the prevalences.

To compare effectiveness and costs of screening on elevated albuminuria in pharmacies and in GP-care, the costs for the targeted screening strategies in both pharmacies and GPs will be calculated.

For each approach, all costs associated with the screening will be added and divided by the total number of subjects identified with confirmed elevated albuminuria. A screening-

approach will be considered more effective than the other if the costs per identified patient are  $\geq 10\%$  lower.

Frequencies of cardiovascular monitoring and treatment changes are summarized as numbers and percentages with 95% confidence intervals.

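### Primary endpoint 1 gives a UACR threshold without saying how many occasions, other text requires two, and the third test appears only in the Summary, so the case definition is not fixed

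*Protocol*

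**What the plan says.** **The endpoint and its analysis.** Protocol section 9.1.1, and the endpoint list in the Summary, define primary endpoint 1 as "Elevated albuminuria, defined as a urinary albumin creatinine ratio (UACR", followed by the threshold of 3.0 mg/mmol or more. Neither place says how many samples must reach it. Section 11 reports the overall prevalence of elevated albuminuria, again without a qualifier. For the cost endpoint, the same section says that costs are "divided by the total number of subjects identified with confirmed elevated albuminuria".

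**Where two occasions are required.** The study methods in the Summary define elevated albuminuria as the same threshold "on two occasions in accordance with the prevailing primary care guideline". Section 4.2 ties confirmation to the same rule: "mg/mmol on two occasions), subjects are invited for an elaborated screening visit with a researcher".

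**Where the word means the first result.** Section 8.1.1 states the threshold and then calls for a confirmatory test when albuminuria is elevated, because of intra-individual and biological variation. Section 9.3 reads likewise: "If albuminuria is elevated, subjects receive a second PeeSpot to perform a confirmational measurement".

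**The third test.** The Summary has it twice: "If not confirmed, they will receive a third collection device" in the study methods, and "If the confirmational measurement is negative, a third measurement is needed" in the paragraph on burden and risk. In the body, section 4.1 says what follows "If this second measurement is also elevated", and stops there.

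**The waiver.** The Summary and sections 4.1, 8.1.1 and 9.3 drop the second PeeSpot when a general-practice value from the previous 11 months was also elevated.

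**The concern.** Estimating this prevalence is primary objective 1, and secondary endpoints 1 and 2 (unrecognized and persistent disease) are built on the same term. Two separate gaps affect it.

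First, the protocol uses elevated albuminuria both for one result above the threshold and for a confirmed state. An analyst who follows 9.1.1 and the prevalence sentence in section 11 to the letter would count everyone above the threshold. The cost endpoint would count only confirmed subjects, so the two primary results would not describe the same cases.

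Second, the test sequence differs between the Summary and the body. Staff working from sections 4.1 and 9.3 would send two devices at most, and staff working from the Summary would send a third after a normal second result. This affects the prevalence numerator, the number of identified patients in the cost ratio, the device and laboratory costs in Table 1, and progress towards the target of 112 examined patients. It cannot be repaired at analysis, because a third sample that was never requested does not exist.

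**Working it through.** **1. Is there a figure to reproduce?** No. Section 5.4 gives the target of 112 and the 6300 eligible patients without a formula, prevalence or precision. No sample size, power or alpha depends on this point.

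**2. The passages side by side.**

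| Place | Occasions stated | Third test |
|---|---|---|
| Summary, study methods | Two | Yes |
| Summary, burden and risk | Confirmation required | Yes |
| Summary, endpoint list | Not stated | Not mentioned |
| 4.1 | Second must also be elevated; no path if it is not | Not mentioned |
| 4.2 | Two | Not mentioned |
| 8.1.1 | Threshold, then a confirmatory test | Not mentioned |
| 9.1.1, endpoint 1 | Not stated | Not mentioned |
| 9.3 | Second PeeSpot after an elevated first | Not mentioned |
| 11, prevalence | Not stated | Not mentioned |
| 11, cost | Confirmed | Not mentioned |

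**3. How far the readings can diverge (illustration only).** The documents give no variances and no retest results, so every input here is an assumption. Take log UACR as a person's own level plus independent test-to-test noise, both normal, with between-person SD σb and within-person SD σw. Set the cut-off so that 10% are elevated on the first test:

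- k = 1.2816 × √(σb² + σw²), on the log scale relative to the mean
- for a person at level b, the chance that any one test is elevated is p = Φ((b − k)/σw)
- A, first test only: E[p] = 10%
- B, first and second both elevated: E[p²]
- C, first elevated, then the second or, failing that, the third: E[p² + p²(1 − p)]

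| σb | σw | A | B | C | A/B | A/C | C/B |
|---|---|---|---|---|---|---|---|
| 1.4 | 0.3 | 10.0% | 7.9% | 8.8% | 1.26 | 1.13 | 1.11 |
| 1.1 | 0.3 | 10.0% | 7.4% | 8.5% | 1.35 | 1.18 | 1.15 |
| 1.1 | 0.5 | 10.0% | 5.9% | 7.4% | 1.68 | 1.35 | 1.25 |
| 1.1 | 0.7 | 10.0% | 4.8% | 6.5% | 2.09 | 1.55 | 1.35 |
| 0.8 | 0.7 | 10.0% | 3.7% | 5.4% | 2.73 | 1.86 | 1.47 |

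The first and last rows are the extremes over σb 0.8 to 1.4 and σw 0.3 to 0.7.

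**4. A check without the log-normal model.** Let c be the chance that the second test is elevated given an elevated first, and d the chance that the third is elevated given elevated then normal. Then B = 10% × c and C = 10% × (c + (1 − c) × d). With assumed c = 0.5 to 0.8 and d = 0.2 to 0.4:

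- B = 5.0 to 8.0%
- C runs from 10% × (0.5 + 0.5 × 0.2) = 6.0% to 10% × (0.8 + 0.2 × 0.4) = 8.8%

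**5. Against sampling error.** If 20 to 50% of the 6300 respond (assumed), n = 1260 to 3150. The 95% half-width at 10% is 1.96 × √(0.1 × 0.9/n), which is 1.7 to 1.0 percentage points. In the model, A exceeds B by 2.1 to 6.3 points, more than that half-width throughout. C exceeds B by 0.9 to 1.7 points, about the same size as it.

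**The case against.** The strongest reply is that the intended case is reasonably clear. The Summary contains an explicit two-occasion definition tied to the primary care guideline, section 4.2 applies it, section 8.1.1 requires a confirmatory test straight after stating the threshold, and the cost analysis says confirmed. On this view the endpoint sentence is incomplete and does not compete with the definition. Much of this stands. A reader might infer that 9.1.1 prescribes a single test, but neither it nor 8.1.1 says so; both are silent on the number of occasions. What remains is that neither the endpoint nor the prevalence sentence carries the requirement, while the cost sentence in the same section does.

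On the third test, a reader might infer that the body makes a positive, negative, positive subject a non-case. It does not say that. Such a subject would meet the two-occasion rule of 4.2 if the third sample were taken. The body text is silent on what follows a normal second result, and Figure 2, which is not shown, may depict a third device. The gap is therefore between the Summary and the body text only. It still matters, because following 4.1 and 9.3 as written yields no third sample.

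A reader might also infer that first-positive subjects who never return a second device are counted as non-cases. Nothing in the protocol says so, and handling of such missing results can properly be left to a statistical analysis plan.

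**Conclusion.** The concern holds as two gaps in wording: an endpoint and a prevalence analysis that omit the confirmation required elsewhere, and a third test that the Summary requires and the body text does not contain. The documents do not support a claim of three rival definitions.

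In the illustration, first-test prevalence is about 1.3 to 2.7 times the two-of-two figure and 1.1 to 1.9 times the two-of-three figure, and the third test raises the two-of-two case count by about 11 to 47%. These ranges rest on the assumed 10% first-test positivity, the assumed variances and the log-normal form. The ordering of the three figures does not depend on those values: requiring confirmation cannot raise the count, and a deciding third test cannot lower the two-of-two count. The gap between first-test and two-of-two prevalence exceeds the assumed sampling error, and the effect of the third test is of similar size to it. Because this is the first primary endpoint and uncollected samples cannot be recovered, the protocol itself should be corrected.

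**What to change.** 1. In 9.1.1, the Summary endpoint list and the prevalence sentence of section 11, define primary endpoint 1 as confirmed elevated albuminuria: 3.0 mg/mmol or more on two occasions. State that an elevated general-practice value within 11 months counts as one of the two, as the protocol already provides. Say that this is the same case as in the cost endpoint.
2. Report first-test positivity separately, under its own name.
3. Reconcile the second- and third-test sequence between the Summary and sections 4.1, 4.2, 8.1.1 and 9.3, including what follows an elevated first and a normal second result. One stated sequence should determine who is a case and which tests are costed.

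The cost is wording in these sections. The headline prevalence will be lower than a first-test figure would be. If the agreed sequence includes the third test, its devices and laboratory work belong in the Table 1 costs.
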